### Secondary outcomes

1. Resolution of skin lesions
2. Recurrence of reaction manifest as skin reactions.

## Sample size

The sample size calculation was based on the expected improvements in the combined scores (skin, sensory & motor) that the addition of azathioprine to prednisolone would produce. It was calculated that the addition of azathioprine would produce a 25% improvement in the combined scores. This would be a score of 4 allowing for an alpha of 0.05 and beta of 0.80, the minimum sample size is calculated as follows:

n=2x[(Zα +Z1-β)xSD)/ d]2 =2x[(1.96+0.842))x2)/1]2 = 63 per group.

We assumed a ‘lost to follow up’ rate of 15%, and dropout rate due to adverse reactions of 10 %,so minimum of 78 patients would be required per arm, and a total of 312.

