## Patient outcome measures

### Primary outcomes

1. **Recovery of nerve function**

- Absolute improvement in nerve function as measured by Voluntary Muscle testing (one point improvement in VMT score) and Sensory testing (two point improvement in ST score) using standard methods as defined in the field manual.

1. **Recurrence of neuritis during or after treatment**

- Recurrence of neuritis is defined as a new nerve function impairment presenting in the form of a decrease in VMT score by one point and an ST score by more than 2 points either during the study period or during the follow up period and present for two consecutive testings.

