## Statistical analysis

The primary analysis will be a comparison of azathioprine plus prednisolone with prednisolone alone for achieving the primary outcome following the “intention to treat” principle. Intention to treat analysis will also be performed for the secondary outcomes.

Analysis of endpoints, comparing time to event in the four arms will be performed.

Pre-planned sub group analysis will be performed for the following subgroups (male, female; MB, PB; previous T1R, new T1R).

A secondary on treatment analysis will be performed to explore the requirement of additional steroids as well as adverse effects with these drugs.

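### The stated 80% power belongs to a combined skin, sensory and motor score that is not a trial outcome, so it does not apply to the two primary outcomes

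*Protocol*

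**What the plan says.** The Sample size section states that the calculation was "based on the expected improvements in the combined scores (skin, sensory & motor"). It assumes that "addition of azathioprine would produce a 25% improvement in the combined scores", and continues "This would be a score of 4 allowing for an alpha of 0.05 and beta of 0.80". The formula line ends "2x[(1.96+0.842))x2)/1]2 = 63 per group". After allowances for loss to follow-up and adverse reactions the total is 78 per arm, 312 in all.

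The Primary outcomes section lists two outcomes. The first is recovery of nerve function: a one-point gain on voluntary muscle testing (VMT) and a two-point gain on sensory testing (ST). The second is "Recurrence of neuritis during or after treatment", a fall in those scores present at two consecutive tests. Resolution of skin lesions and recurrent skin reactions are secondary outcomes.

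The Statistical analysis section makes the primary analysis a "comparison of azathioprine plus prednisolone with prednisolone alone for achieving the primary outcome", in the singular. It adds a time-to-event comparison across the four arms.

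**The concern.** The only alpha and power in the protocol are attached to the mean of a combined score. That score appears nowhere outside the Sample size section. It overlaps with recovery through its sensory and motor parts, but it also contains skin, it is a mean rather than a threshold, and it says nothing direct about recurrence. No conversion from a one-point score difference to a recovery or recurrence rate is given.

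Eligibility widens the gap. The Inclusion Criteria admit patients with recurrent reactional skin lesions and no neuritis. Such patients can move a score with a skin component, but they may have little nerve function to recover.

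What is at stake is how the result is read. A null finding on recovery or recurrence would be taken as coming from a test with 80% power, which the protocol does not support.

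**Working it through.** **1. The plan's own figure.** Inputs from Sample size: d = 1, SD = 2, z = 1.96 and 0.842.

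n = 2 × [(1.96 + 0.842) × 2 / 1]² = 2 × 5.604² = 62.81, rounded up to 63 per group. Power at 63 per group is 80.1%. The arithmetic is right for a single two-group comparison of mean scores. The phrase "allowing for an alpha of 0.05 and beta of 0.80" must mean power of 0.80, since 0.842 is the normal quantile for 80% power.

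**2. What was sized against what is tested.**

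| | Sample size section | Outcomes and analysis sections |
|---|---|---|
| Variable | Combined skin, sensory and motor score | Recovery (VMT and ST thresholds); recurrence (confirmed event) |
| Skin | Included | Secondary only |
| Scale | Difference in means | Responder or event |
| Number of primary outcomes | One | Two listed; the analysis text refers to one |
| Contrast | Two groups of equal size | Azathioprine plus prednisolone (three arms) against prednisolone alone |

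**3. Illustrative power for the listed outcomes.** The protocol gives no control rate or effect for either outcome, so everything in this step is assumed.

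- Control recovery of 50%, 60% and 70%. These are the improvement figures quoted in Background, which are not shown to use this trial's definition of recovery.
- Control recurrence of 50%. This is the share needing further steroids on a 12-week regimen in Background, used as a stand-in.
- 63 evaluable per arm, as the protocol intends; 63 against 189 (3 × 63) when the azathioprine arms are pooled.
- Two-sided alpha 0.05, two-proportion normal test.

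Power = Φ[(|p2 − p1| − 1.96 × se0) / se1], where se0 = √[p̄(1 − p̄)(1/n1 + 1/n2)], with p̄ the overall proportion, and se1 = √[p1(1 − p1)/n1 + p2(1 − p2)/n2].

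Worked case, 60% against 75%, 63 per arm: p̄ = 0.675; se0 = √(0.675 × 0.325 × 2/63) = 0.0835; se1 = √[(0.24 + 0.1875)/63] = 0.0824. Power = Φ[(0.15 − 1.96 × 0.0835)/0.0824] = Φ(−0.165) = 43%.

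Two ways of carrying the planned effect over to a recovery rate are shown. The first treats the 25% as a relative gain in the rate, p2 = 1.25 × p1. The second keeps the standardised effect d/SD = 1/2 as a shift in an assumed normal response, p2 = Φ[Φ⁻¹(p1) + 0.5].

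| Outcome and conversion | Control | Azathioprine | Pairwise | Pooled 63 vs 189 |
|---|---|---|---|---|
| Recovery, 25% relative gain | 50% | 62.5% | 29% | 42% |
| | 60% | 75% | 43% | 62% |
| | 70% | 87.5% | 67% | 86% |
| Recovery, 0.5 SD shift | 50% | 69% | 59% | 78% |
| | 60% | 77% | 56% | 76% |
| | 70% | 85% | 51% | 71% |
| Recurrence, 25% relative fall | 50% | 37.5% | 29% | 42% |

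**4. Detectable difference.** Pairwise at 63 per arm with 80% power and alpha 0.05, recovery would have to rise from 50% to 74%, 60% to 82%, or 70% to 90%. Recurrence would have to fall from 50% to 26%, 40% to 18%, or 30% to 10%. That is about 20 to 24 percentage points throughout.

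**The case against.** **The score is related to recovery, and pooling helps.** Both are true. If the three azathioprine arms are pooled, the planned one-point difference has 93% power at alpha 0.05 and 88% at 0.025. But this is still power for the score, and the Statistical analysis section does not say that the arms are pooled.

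**The illustrative figures depend on the conversion.** This stands. The 25% is an improvement in a score, and reading it as a relative gain in a rate is an assumption; the 0.5 SD shift gives a narrower and mostly higher range. One pooled case reaches 86%. The figures therefore do not show that the trial is underpowered or could not detect an effect, only that 80% has not been established.

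**A reader might infer that a score of 4 contradicts d = 1.** With d = 4 the formula would give 2 × (2.802 × 2/4)² = 3.9, or 4 per group. But 25% of 4 is 1, so the sentence agrees with the formula if 4 is the reference score. It is unclear, not shown to be wrong.

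**A reader might also infer an inflated type I error.** Testing each of three arms against control on both outcomes would be six tests, and the protocol does not plan these. Nor does it say that success on either outcome alone would count. How alpha is divided may be set in a statistical analysis plan that is not at hand. What the protocol itself shows is two primary outcomes in one section and a single one in another.

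**Conclusion.** The point holds as a mismatch within the protocol. The calculation is arithmetically correct for a one-point, two-group difference in a combined score, but that score is not an outcome of the trial, so the 80% power does not apply to the primary analysis. This conclusion rests on the protocol's text alone and needs no assumed rates.

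The size of the gap is less certain. Across the scenarios examined, power for recovery runs from 29% to 67% pairwise and from 42% to 86% pooled; for recurrence of 50% against 37.5% it is 29% pairwise and 42% pooled. These figures assume the control rates, the conversion of the effect, 63 evaluable per arm, and alpha 0.05 for each outcome. They give a range and do not define a corrected sample size.

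**What to change.** Align the Sample size, Primary outcomes and Statistical analysis sections in one of two ways.

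- **Keep the listed primary outcomes.** Replace the combined-score paragraph with the power or detectable difference for recovery and for recurrence at the planned size. State the contrast (pairwise or pooled), the alpha used for each of the two outcomes, and the assumed control rates with their source. For example, at 63 per arm, 80% power and alpha 0.05, about 20 to 24 percentage points are detectable pairwise.
- **Keep the combined score.** If it is the real target, define how it is built and name it as the primary outcome.

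Under either option, make the Statistical analysis section say which primary outcome or outcomes it means. If the combined score is kept, also say whether 4 is the reference value of which 25% gives d = 1, and write power of 0.80 in place of beta.

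Whether to pool the arms, how to divide alpha, and how to rank the comparisons of azathioprine duration are the sponsor's choices; the text has only to state them.

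The cost is wording, and probably a less favourable stated power. No extra patients are needed.

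### Enrolling 78 per arm does not leave the 63 evaluable patients the sample-size formula calls for once the protocol's own 15% and 10% losses are taken off

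*Protocol*

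**What the plan says.** The Sample size section of the protocol sets the error rates as "alpha of 0.05 and beta of 0.80" and works out the group size as "n=2x[(Zα +Z1-β)xSD)/ d]2 =2x[(1.96+0.842))x2)/1]2 = 63 per group". The outcome behind this is a combined skin, sensory and motor score.

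It then allows for two kinds of loss, 15% lost to follow-up and a "dropout rate due to adverse reactions of 10 %,so minimum of 78 patients would be required per arm, and a total of 312". It shows no formula for the step from 63 to 78.

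Three other sections bear on the point:

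- **Statistical analysis** sets intention to treat for the primary comparison of azathioprine plus prednisolone with prednisolone alone.
- **Patient follow-up procedure**, items 5 to 7, removes patients from the study for not returning, for missing two visits in a row, or for four weeks of missed treatment.
- **Management of Complications**, item 5, continues nerve function assessment for a patient who discontinues because of pregnancy.

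**The concern.** A minimum enrolment is meant to leave the calculated number of evaluable patients after the expected losses. Losses of 15% and 10% come to about a quarter of those enrolled, yet 78 exceeds 63 by only 15 patients, which is 19.2% of 78. That pattern is typical of multiplying the required number by one plus the loss rate when it should be divided by the fraction retained.

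What is at stake is whether the stated enrolment supports the stated power on the protocol's own inputs. The section also gives beta as 0.80, which taken literally would mean 20% power, so it needs checking which was used.

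**Working it through.** **Inputs, all from the Sample size section:** Z values 1.96 and 0.842; SD 2; difference d = 1; losses of 15% and 10%; 78 per arm, 312 in total. Four equal arms follow from the Randomization section. Whether d = 1 and SD = 2 suit the outcomes is not tested here; they are taken as given.

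**1. Reproduce the 63.** n = 2 x [(1.96 + 0.842) x 2 / 1]² = 62.8, rounded up to 63. The formula evaluates as stated. The value 0.842 is the normal quantile for 80% power, so power 0.80 (beta 0.20) was used.

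**2. Reproduce the 78.** The total agrees: 4 x 78 = 312. Two multiplying-up routes land on or near 78:
- losses added (25%): 63 x 1.25 = 78.75, which gives 78 if cut down;
- losses in sequence (1 - 0.85 x 0.90 = 23.5%): 63 x 1.235 = 77.8, which rounds to 78.

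**3. Patients left from 78 per arm.**
- Additive: 78 x 0.75 = 58.5.
- Sequential: 78 x 0.85 x 0.90 = 59.7.
- Largest loss that still leaves 63: 1 - 63/78 = 19.2%.

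**4. Enrolment that would leave 63.**

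| Reading of the losses | Calculation | Per arm | Total | Excess over 312 |
| --- | --- | --- | --- | --- |
| Additive | 63 / 0.75 = 84.0 | 84 | 336 | 24 |
| Sequential | 63 / 0.765 = 82.4 | 83 | 332 | 20 |

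**5. Power for one arm against control.** With d/SD = 0.5, power = Φ(0.5 x √(n/2) - 1.96), n being the evaluable number per arm.

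| Evaluable per arm | Origin | Normal formula | t test |
| --- | --- | --- | --- |
| 63 | as required | 80.1% | 79.5% |
| 59.7 | 78, sequential losses | 78.0% | 77.3% |
| 58.5 | 78, additive losses | 77.2% | 76.5% |

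**6. If only the 15% were lost to the analysis.** 78 x 0.85 = 66.3 evaluable, and the normal formula gives 82.1%. This assumes that patients who stop for adverse reactions are still assessed, and it ignores any dilution of the effect from stopping drug.

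**7. If the three azathioprine arms were pooled against control.** With the same d and SD, 58.5 controls against 3 x 58.5 = 175.5 gives a standard error of 2 x √(1/58.5 + 1/175.5) = 0.302 and power Φ(1/0.302 - 1.96) = 91.2%. With 59.7 controls it is 91.7%.

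**The case against.** The strongest reply is that the shortfall barely matters. The loss is 2 to 3 points of power. The primary analysis as worded may pool three arms against one, and on the same inputs that comparison would have about 91-92%. The formula also concerns a combined score that includes skin, whereas the listed primary outcomes are nerve function recovery and recurrence of neuritis, with skin secondary.

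Much of this stands, and it limits the point. A reader might infer that the trial's primary analysis has only 77% power, or that more patients are needed. The documents support neither. The 77-78% describes one pairwise comparison on one score, and it was not calculated for the listed primary outcomes. But pooling does not repair the paragraph, which calculates a two-group size and applies it to each arm. Objective 4 compares azathioprine durations, and there the size of each arm matters.

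A reader might also infer that 63 was multiplied by 1.25 and rounded down. That is plausible but unproven: the protocol shows no inflation formula, and 63 x 1.235 gives 78 by ordinary rounding. The shortfall does not depend on which route was taken.

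Finally, it may be said that under intention to treat the 10% who stop for adverse reactions are not lost, so 312 already gives about 82%. As the protocol stands, that figure is not available. The Sample size section counts both rates as losses, and item 7 of Patient follow-up procedure removes patients after four weeks of missed treatment. The pregnancy provision shows that assessment after stopping drug is possible, but the protocol does not extend it to adverse reactions.

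**Conclusion.** The point holds as a narrow arithmetic error. On the protocol's own inputs, 78 per arm leaves 58.5 or 59.7 evaluable patients where 63 are called for, 5 to 6 fewer enrolled per arm than needed and 20 to 24 fewer in total. Power for one arm against control on the combined score is 77.2% to 78.0% by the protocol's formula, against the 80% intended. This assumes d = 1 and SD = 2 as the section uses them, a two-sided 5% level as implied by 1.96, and both losses removing patients from the analysis, as the section itself treats them.

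The practical effect is small and is no reason to enlarge the trial. It should still be corrected, because the stated enrolment does not deliver the stated power. The beta wording is a labelling slip with no numerical effect: a reader might take it as 20% power, but the 0.842 in the formula rules that out.

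**What to change.** Keep 312 and correct the Sample size paragraph:

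- State that 78 per arm leaves about 58 to 60 evaluable patients after the assumed losses, and that power is about 77-78% for a comparison of one azathioprine arm with control on the combined score, with d = 1 and SD = 2.
- Show the inflation step, and say whether the two losses add or apply in sequence.
- Replace the stated beta with power 0.80 (beta 0.20).

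This costs one paragraph and a slightly less favourable figure, with no extra patients.

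An alternative is to state about 66 evaluable per arm and about 82% power, before any dilution from stopping drug. That is open only if the removal rules in Patient follow-up procedure are first reconciled with the intention-to-treat principle in Statistical analysis, so that patients who stop for adverse reactions stay in outcome assessment. This changes follow-up procedure at four hospitals and is more than a matter of wording. Until it is done, the 82% should not be stated.

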## Statistical analysis

The primary analysis will be a comparison of azathioprine plus prednisolone with prednisolone alone for achieving the primary outcome following the “intention to treat” principle. Intention to treat analysis will also be performed for the secondary outcomes.

Analysis of endpoints, comparing time to event in the four arms will be performed.

Pre-planned sub group analysis will be performed for the following subgroups (male, female; MB, PB; previous T1R, new T1R).

A secondary on treatment analysis will be performed to explore the requirement of additional steroids as well as adverse effects with these drugs.

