***Methods***

## Study design and setting

This study is a randomized double blind controlled clinical trial with continuous enrollment of individuals into 4 arms of the study.

The participating centres are:

- TLM hospital Faizabad, (UP)
- TLM Hospital Shahdara (Delhi).
- TLM Hospital Purulia (West Bengal)
- TLM Hospital, Champa

The study will compare Azathioprine when used with prednisolone against prednisolone used alone, for the treatment of acute neuritis and recurrent reactional skin lesions.

Azathioprine will be used at three durations of 24 weeks, 36 weeks and 48 weeks. All patients will complete 48 weeks of treatment comprising Prednisolone (20 weeks standard therapy) + Azathioprine/Placebo.

Clinical measurement of nerve function and skin appearance will be used to determine the outcomes.

##

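### The primary analysis is worded as one comparison on one outcome, but the protocol has two primary outcomes and three azathioprine arms, so the deciding test is not fixed

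*Protocol*

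**What the plan says.** The Statistical analysis section defines the primary analysis as a "comparison of azathioprine plus prednisolone with prednisolone alone for achieving the primary outcome", by intention to treat. The outcome is in the singular and the comparison is two-way.

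Three other places do not match that sentence:

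- **Outcomes.** Primary outcomes has two numbered entries. The first is recovery of nerve function, judged by VMT and ST point gains. The second is recurrence: "Recurrence of neuritis is defined as a new nerve function impairment", shown by a fall in both scores. No either/both rule is given.
- **Arms.** Study design and setting says "Azathioprine will be used at three durations of 24 weeks, 36 weeks and 48 weeks". Study interventions confirms three interventional arms and one control arm.
- **Sample size.** The calculation is a two-group formula with equal groups, "2x[(1.96+0.842))x2)/1]2 = 63 per group", described as "allowing for an alpha of 0.05 and beta of 0.80". It is built on "expected improvements in the combined scores (skin, sensory & motor", a combined score that is neither primary outcome.

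The analysis section then adds, without ranking it, "Analysis of endpoints, comparing time to event in the four arms will be performed", followed by three pairs of subgroups. Objective 4 under Study Aims asks for a comparison of azathioprine durations.

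**The concern.** A primary analysis should let a reader say in advance which result will decide the trial. Here the sentence admits at least two readings of the contrast (arms 2–4 pooled against arm 1, or each of arms 2, 3 and 4 against arm 1) and at least two readings of success (either outcome, or both). The wording of the sentence points to pooling. The sample size formula points to one arm against control.

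Two things are at stake. First, if the choice is made after the data are seen, or if any significant result is accepted, the 0.05 used in the sample size does not describe the trial's error rate. Second, the two readings of the contrast can reach different conclusions from the same data, most clearly when only one duration works.

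**Working it through.** **1. The plan's own figure.** Inputs from Sample size: z = 1.96 (two-sided 0.05), z = 0.842 (power 0.80, which the text calls beta), SD = 2, d = 1.
n = 2 × [(1.96 + 0.842) × 2 / 1]² = 62.8, so 63 per group. The figure reproduces. It is the size for one arm against one arm, one outcome, with no division of alpha.

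**2. False-positive rate under no effect.** Inputs: four equal arms (Randomization), two primary outcomes, each test two-sided at 0.05, any one significant result counted as success. The last two conditions are assumptions. The correlation between the outcomes is not given, so a range is shown. Results are from simulated null trials with a shared control arm.

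| Tests counted | Correlation 0 | 0.5 | 0.8 | 1 |
|---|---|---|---|---|
| Pooled arms v arm 1, two outcomes | 9.7% | 9.1% | 7.8% | 5.0% |
| Three arms v arm 1, one outcome | 12.5% | 12.5% | 12.5% | 12.5% |
| Three arms v arm 1, two outcomes | 23.5% | 22.0% | 19.0% | 12.5% |

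Check on the first cell: two independent tests give 1 − 0.95² = 9.75%.

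If both outcomes must succeed on one contrast, a false claim requires the test of a null outcome to be significant at 0.05, so the rate is at most 5%.

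**3. How far the two contrasts diverge.** This uses the Sample size figures (d = 1, SD = 2, 63 per arm). Power = Φ(effect/SE − z).

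- Pairwise SE = 2 × √(1/63 + 1/63) = 0.356. Pooled SE = 2 × √(1/63 + 1/189) = 0.291.
- Only arm 4 works: the pooled effect is 1/3, so power = Φ(0.333/0.291 − 1.96) ≈ 21%. Arm 4 against arm 1: Φ(1/0.356 − 1.96) ≈ 80%.
- All three durations work equally: pooled power = Φ(1/0.291 − 1.96) ≈ 93%. By simulation, in about 32% of all trials the pooled test is significant while at least one pairwise test is not. That would look like a duration effect where none exists.

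**4. Cost of splitting alpha.** With 63 per group and the same d and SD, one pairwise test has about 71% power at 0.05/2 = 0.025 and about 57% at 0.05/6. Restoring 80% would take 77 and 97 per group. The pooled contrast at 0.025 has about 88%.

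Steps 3 and 4 are indicative only, because d and SD belong to the combined score. The protocol gives no rate, effect or SD for either primary outcome.

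**The case against.** The strongest reply has four parts.

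- **Alpha rules belong in the SAP.** Test-level alpha and multiplicity rules are commonly left to that document, which is not at hand. This stands: the lack of an alpha split in the protocol is not a finding by itself. What remains is that the protocol does define its primary analysis, in words that do not fit its own outcomes and arms.
- **The protocol never says that any one success is enough.** This also stands. A reader might infer that every comparison is made at full alpha and that the trial's error rate is therefore close to a quarter. The document does not support that. The 0.05 appears only in Sample size, and no success rule is written.
- **Only one analysis is called primary.** The four-arm time-to-event comparison is a separate sentence without that label, and the subgroups are labelled as such. On the pooled reading only the two outcomes can inflate the error, to between 5% and 9.75%. Counting the four-arm test, the between-duration comparisons or within-subgroup tests gives larger totals, but it treats as decisive what the protocol does not. Pooling is the natural reading of the sentence, but the pairwise sample size keeps the other reading open.
- **Choosing the pooled contrast is a design preference.** The Background says that azathioprine was given for too short a time in the earlier Nepal trial, and objective 4 compares durations. A pooled test dilutes the effect if only the longest course works. This is fair, and the sponsor must weigh it. It does not remove the need to name one contrast.

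**Conclusion.** The point holds as an internal contradiction that leaves the deciding test undetermined: one outcome in the analysis sentence against two in the outcome list, one comparison against three azathioprine arms, and a sample size for a single pairwise test at an unsplit two-sided 0.05.

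The size is conditional on each test being done at 0.05 and any one success counting. It is then about 8–10% for the pooled contrast on two outcomes and about 19–24% for three pairwise contrasts on two outcomes, over outcome correlations from 0.8 to 0. Under a both-must-succeed rule on one contrast, error is not inflated above 5%. A reader should not take the upper figures as the trial's actual error rate, nor the power figures as the power for recovery or recurrence.

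The trial can be analysed properly once the wording is settled. This should be corrected before unblinding.

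**What to change.** **Statistical analysis section**

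1. Name the primary contrast. Arms 2, 3 and 4 pooled against arm 1 is the natural reading of the present sentence.
2. Test it on both primary outcomes with overall two-sided 0.05 control. Holm is suitable if no further confirmatory claims follow.
3. State the rank of the duration comparisons in objective 4. If they are to be confirmatory, give each outcome a fixed 0.025. Only after that outcome's pooled test succeeds, compare each duration with arm 1 by Holm or Dunnett within the same 0.025, and pass no alpha between outcomes. Each outcome then contributes at most 0.025: if its pooled null is true, the gate limits the error, and if not, Holm or Dunnett does. Holm across outcomes must not be combined with spending the same share again on durations. In a simulated case with a 2-point effect in arms 3 and 4 on one outcome only, that gave a family-wise error of about 7.0% (6.7% at correlation 0.5).
4. Label the four-arm time-to-event test and the subgroups as supportive, and judge subgroups by interaction tests.

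**Sample size section**

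State that 63 per group gives 80% power only for one unadjusted pairwise comparison on the combined score, and about 71% at 0.025.

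**Cost**

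Wording only, with no added patients or data. The price of the pooled contrast is weak power if only one duration works: about 21% at 0.05 on the Sample size figures, and less at 0.025. A sponsor who prefers a pairwise primary contrast can choose it, but must then adjust for three arms and two outcomes and recheck the sample size (97 per group for a six-way Bonferroni split on the same d and SD).

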Azathioprine is an immuno suppressant that has been used in other immune mediated diseases both as monotherapy and in combination with prednisolone as a steroid-sparing agent.20 It is metabolized to mercaptopurine by the enzyme thiopurine methyltransferase. It is widely used for organ transplant recipients and to treat a number of autoimmune conditions, usually when corticosteroid therapy alone provides inadequate control. 21

A recent trial conducted in Nepal using a three-month course of Azathioprine along with Prednisolone showed that addition of Azathioprine reduces the corticosteroid requirement for treatment of type 1 reactions. Although the clinical outcomes were similar for patients treated with either the prednisolone/azathioprine combination or prednisolone alone, the overall dose of prednisolone was less in those on the combined regimen.16 One of the shortcomings of the Nepal study was that the azathioprine was not used for a long enough duration.

Adverse effects due to azathioprine may occur in upto 15% of patients.21 The commonest adverse reactions that occur with azathioprine are nausea and vomiting and mucosal ulcers, occurring in 60% of patients.22 Azathioprine also causes significant bone marrow suppression (upto 5%) and can potentially cause leucopenia (3.8%), thrombocytopenia (2%) and even pancytopenia (0.4%).23 There may be an increased risk of infections and different malignancies. Pancreatitis, skin rashes and drug fever have been reported on rare occasions.24 Use of azathioprine in pregnancy has shown that the placenta may act as a barrier to its passage and current evidence of safety in pregnancy is reassuring.25, 26

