## Introduction:

## Study Aims

The primary aim of this study is to compare the neurological outcomes in patients with type 1 reactions and recurrent type I reactions in skin lesions, when they are treated with either Azathioprine in addition to a 20-week course of prednisolone or prednisolone alone.

The objectives of the study are: -

1. Improves dermatological outcomes in Type 1 reactions.

2. Improves neurological outcomes in Type 1 reactions and neuritis

3. Reduces the recurrence rate (i.e. requirement for further treatment with steroids) in patients with T1R and neuritis.

4. To compare the effectiveness of different duration of treatment with Azathioprine in T1R and neuritis.

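### Objective 3 equates recurrence with the need for further steroids, but that measure is in neither outcome list and its only named analysis is an exploratory on-treatment one

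*Protocol*

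**What the plan says.** - **Study Aims, objective 3:** "Reduces the recurrence rate (i.e. requirement for further treatment with steroids) in patients with T1R and neuritis". Recurrence is thus stated in terms of steroid need.
- **Primary outcomes:** recurrence of neuritis is defined by a fall in both the voluntary muscle test (VMT) score and the sensory test (ST) score. Steroid use is not part of the definition.
- **Secondary outcomes:** resolution of skin lesions, and "Recurrence of reaction manifest as skin reactions". Steroid use is absent here too.
- **Statistical analysis:** the main comparison is "for achieving the primary outcome following the “intention to treat” principle", and "Intention to treat analysis will also be performed for the secondary outcomes".
- **Statistical analysis, on steroid need:** "A secondary on treatment analysis will be performed to explore the requirement of additional steroids as well as adverse effects with these drugs". This is the only sentence in that section that mentions additional steroids.
- **Statistical analysis, time to event:** "Analysis of endpoints, comparing time to event in the four arms will be performed". It names neither the endpoints nor the set of patients.

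**The concern.** Intention to treat is assigned to the listed outcomes. Steroid need is not listed, so the protocol ties the measure named in objective 3 to a comparison that depends on what happens to patients after randomisation. Treatment allocation is still randomised, but the on-treatment selection is not protected by it.

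The measure matters to the rationale. The Background reports that clinical outcomes in the earlier Nepal trial were similar with and without azathioprine, and that the advantage was that "the overall dose of prednisolone was less in those on the combined regimen". It also gives flare-up on tapering and steroid dependence as reasons for seeking an adjunct. If the groups compared differ in who stopped treatment, a difference in steroid need could reflect that selection and not azathioprine.

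**Working it through.** **The plan's own figure.** The protocol calculates nothing for steroid need. Its sample size reproduces: 2 × [(1.96 + 0.842) × 2 / 1]² = 62.8, so 63 per group. It is based on combined skin, sensory and motor scores, and this point does not rest on it.

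**Can the intention-to-treat outcomes stand in for steroid need?**

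| Place in protocol | Event | Criterion |
| --- | --- | --- |
| Management of Complications, item 1 | Prednisolone stepped up or restarted | Worsening of neuritis or type 1 reaction |
| Definitions, worsening of acute neuritis | Worsening | VMT fall of at least 1 point **or** ST fall of 2 points, at two consecutive tests |
| Primary outcomes, recurrence of neuritis | Recurrence | VMT fall of 1 point **and** ST fall of more than 2 points, at two consecutive tests |

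A patient whose VMT score alone falls by one point meets the worsening definition and is due extra prednisolone, but does not meet the recurrence outcome. The two measures overlap without being the same.

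**How large could the selection effect be?** Let p be the true rate of steroid need in every arm (no azathioprine effect), e the share of azathioprine patients left out, and r the risk among those left out.

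- On-treatment rate = (p − e × r) / (1 − e)
- Bias = e × (p − r) / (1 − e), so it depends on the gap between r and p

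Inputs:
- p = 50%, from the Background (further steroids after a 12-week prednisolone regimen).
- e = 10%, equal to the adverse-reaction dropout in the Sample size section. Placing it in the azathioprine arms alone, with no control patients left out, is my assumption.
- r has no source in the protocol, so a range is shown.

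| r | On-treatment rate with azathioprine | Difference from 50% |
| --- | --- | --- |
| 30% | (0.50 − 0.03) / 0.90 = 52.2% | +2.2 points (against azathioprine) |
| 50% | (0.50 − 0.05) / 0.90 = 50.0% | 0 |
| 70% | (0.50 − 0.07) / 0.90 = 47.8% | −2.2 points |
| 80% | (0.50 − 0.08) / 0.90 = 46.7% | −3.3 points |

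With 3 × 78 = 234 azathioprine patients, less 10%, against 78 controls, a pooled two-proportion z-test at a nominal 5% rejects in about 6% of trials at r = 70%. The same figure applies at r = 30%, in the other direction.

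**The case against.** Several counter-arguments have force.

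- **Objective 3 is not left without a randomised comparison.** A reader might infer that it is. Recurrence by VMT/ST and by skin reaction is analysed by intention to treat, and worsening is what triggers extra steroids. This stands. The gap concerns steroid need itself, for which the table above shows these outcomes are not equivalent.
- **The time-to-event sentence might cover steroid need.** It might, but it names no endpoint or analysis set, while the sentence that does name steroid need says on treatment.
- **On treatment is not defined.** It could mean exclusion, censoring at stopping, or grouping by treatment received. The arithmetic above assumes exclusion. The analysis is also labelled secondary and exploratory. Both points soften the finding. An analysis plan could define the term, but the protocol has already chosen the on-treatment approach for this measure.
- **A much larger bias cannot be supported.** Removing 25% of azathioprine patients and no controls gives (0.50 − 0.25 × 0.70) / 0.75 = 43.3% and (0.50 − 0.25 × 0.80) / 0.75 = 40.0%, a false benefit of 7-10 points. But that 25% is the 15% loss to follow-up plus the 10% adverse-reaction dropout, and the Sample size section applies both to every arm. Removing the 15% from control as well gives (0.50 − 0.15 × 0.70) / 0.85 = 46.5% and (0.50 − 0.15 × 0.80) / 0.85 = 44.7%, leaving about 3-5 points. If losses and risks are equal across arms, the bias is zero.
- **A safety bias in favour of azathioprine is not shown.** Toxicity that leads to stopping occurs on treatment and would be counted. Only events after stopping could be missed, and the protocol gives no figure for them.

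**Conclusion.** The point holds in a limited form. The measure by which objective 3 describes recurrence is missing from both outcome lists, falls outside the stated intention-to-treat rule, and is named only in an exploratory on-treatment analysis. The intention-to-treat recurrence outcomes do not replace it, because the steroid trigger accepts a fall in either score and the outcome requires a fall in both.

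The illustrative bias is about 2-3 points. It assumes a 50% rate in every arm, no true effect, full exclusion of 10% of azathioprine patients and no controls, and a 70-80% risk in those excluded. The 50% comes from a 12-week regimen, whereas this trial uses 20 weeks. A reader might infer that the plan must favour azathioprine. The protocol does not support that: the bias is zero if those excluded have the same 50% risk as everyone else, and it reverses below that. The reason to change the plan is that neither the size nor the direction of the bias can be known in advance.

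**What to change.** 1. Add to the secondary outcomes the need for additional prednisolone (any step-up or restart) to week 48.
2. Compare it by randomised arm in all randomised patients. The time-to-event analysis already planned is a natural place: time to first additional prednisolone, using all data up to each patient's last visit.
3. Keep the on-treatment version as a sensitivity analysis and say what on treatment means.
4. Summarise adverse effects for all patients dosed, including recorded events after stopping.

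The cost is small, but it is more than a change of wording. The Patient follow-up procedure says the clinical visit forms record end points, compliance and adverse effects. It does not say that they record prednisolone changes, so that must be made explicit. Items 5 to 7 of the same section remove patients who miss visits or four weeks of treatment. Those rules must be reconciled with intention to treat, since data after removal would otherwise be missing whatever the analysis is called. No change to treatment is involved.
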